## Sources of costing data

We will collect data from all study sites using a tool adapted from the Male Circumcision Decision-Makers’ Program Planning Tool (DMPPT) ^[[33]](#endnote-32)^ for each of the demand creation strategies (Appendix 22: Costing Instrument). The DMPPT was developed by the USAID/Health Policy Initiative in collaboration with UNAIDS to enable decision-makers to understand the potential cost and impact of various options for scaling up male circumcision services.^28^ The DMPPT has previously been used to undertake costing of male circumcision services in East and Central Africa.^[[34]](#endnote-33)^ We shall use this instrument as our data collection tool to estimate the cost of demand creation and the unit cost of providing VMMC (i.e. cost per adult circumcised) in each of the four study arms.

Table 6 below summarizes the key data sources for the various components of the unit costing tool and the DMPPT.

**Table 6:** Summary of data sources for use in costing

| **Type of Data** | **Source of Data** |
| --- | --- |
| Direct demand creation costs | - Requisitions from the stores to support demand creation. - Payments made by accounts department towards local transport for RAs, production and distribution of IEC materials, road shows, print and electronic media events, and other expenses. - The number of circumcisions done extracted from the VMMC registers. |
| Staffing and compensation | - Cost for hiring and training RAs will be based on actual training expenditure obtained from accounts and HR departments. - For staff involved in recruitment, their salaries, fringe benefits and allowances will be obtained from accounts department. |
| Operational costs | - The operational costs for each VMMC site will be derived from the records at the district level accounts offices. These include rent and utilities, vehicle insurance and maintenance, and communication costs. |
| Administrative and program costs | - We shall apportion the cost of supervision by key staff according to proportionate time spent on study related activities. Costs are salaries, allowances and fringe benefits. Other costs such as external audits, subscription fees to umbrella unions, and payments to statutory bodies shall be apportioned accordingly. |
| Service provision cost | - Service providers, field supervisors and support staff will be tracked in terms of salaries, allowances and fringe benefits; also, cost of VMMC supplies will be tracked, as well as proportional cost of equipment and instruments |

## Costing Data Analysis: Incremental cost-effectiveness ratio (ICER) estimation:

The cost effectiveness analysis will estimate the incremental costs (ΔC) and incremental effects (DALYs averted) (ΔE) attributable to IPC, DSO, IPC+DSO interventions, with reference to routine VMMC service delivery settings. Each will be expressed in terms of an incremental cost effectiveness ratio (ICER; ΔC/ΔE). ^29,^^[[35]](#endnote-34)^ The incremental cost-effectiveness ratios (ICERs) for each intervention shall be the key outcome measures of the model to determine the additional costs and benefits of each strategy over the other. We shall estimate the ICER for additional proportion of men aged 25-39 years accessing VMMC sites as the primary service delivery outcome. The ICER will be computed at a 3% discount rate (to account for time preference of cost and utility) using HIV infections averted and DALYs averted as the incremental benefits. ^[[36]](#endnote-35),^^[[37]](#endnote-36)^ This ratio demonstrates a range of plausible threshold (‘willingness–to–pay (WTP)) values of expenditure for the incremental benefits of respective intervention options.^[[38]](#endnote-37)^

The associated level of uncertainty will be characterized by estimating the cost-effectiveness acceptability curve (CEAC) for each intervention, using Monte Carlo simulations, which estimate the aggregate uncertainty from all inputs. Sensitivity analysis will be undertaken to assess the robustness of conclusions to key assumptions.^29^ We will use multivariate Monte Carlo regressions to estimate the differences in total cost between the settings and to adjust for potential confounders. We will attempt to identify what the cost drivers likely to be affected by the interventions are, how these items should be identified, and ascertain implications of uncertainty surrounding key drivers of cost.

We shall use a hypothetical cohort of 100,000 participants with similar characteristics to evaluate long-term outcome intervention effects using *Monte Carlo simulation approach*. The long-term outcome measures will include improved utility of/satisfaction level with services, improved uptake of services, and quality of outcomes. ^[[39]](#endnote-38),^^[[40]](#endnote-39)^

The incremental cost effectiveness ratio (ICER) of the three interventions will be based on the formulae provided below.

Where

The higher the ICER the less cost effective the intervention program is.

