| Locations eligible for selection | 122 |
| Locations excluded because they are proximal to a previously selected Location | 77 |
| Number of Locations selected for the study | 45 |

**Table 2:** The number of Locations assigned to each study arm by district

|  | **Study Arm** | | | | **Total** |
| --- | --- | --- | --- | --- | --- |
| **District** | **Control** | **IPC** | **DSO** | **IPC+DSO** |  |
| Bondo | 1 | 1 | 1 | 1 | 4 |
| Homabay | 1 | 1 | 2 | 1 | 5 |
| Ndhiwa | 1 | 1 | 2 | 1 | 5 |
| Kisumu East | 1 | 0 | 2 | 1 | 4 |
| Kisumu West | 1 | 1 | 0 | 1 | 3 |
| Nyatike | 1 | 2 | 1 | 2 | 6 |
| Migori | 1 | 0 | 0 | 1 | 2 |
| Rarieda | 1 | 1 | 0 | 0 | 2 |
| Rongo | 0 | 1 | 0 | 2 | 3 |
| Siaya | 1 | 2 | 1 | 2 | 6 |
| Suba | 2 | 1 | 2 | 0 | 5 |
| Totals | 11 | 11 | 11 | 12 | 45 |

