**COSTING VMMC IN THE CONTEXT OF THE INTERVENTIONS (SUB-STUDY 3)**

Study Design: One of the aims of the study is to determine the cost of demand creation, as well as the unit cost of providing VMMC services under each of the demand creation strategies being proposed. Data on costing will be collected across all the study arms. Whereas economic evaluation of service delivery has been conducted in several contexts ^[[32]](#endnote-31)^ there is limited information on cost-effectiveness of various approaches used for recruitment to increase service uptake. We plan to assess the cost-effectiveness of demand creation for VMMC services based on the three interventions. The results will demonstrate the accrued costs and net savings associated with each intervention strategy. This information will support policy and program decisions, guideline formulation, and allocation of scarce resources to scale up effective demand creation approach(es).

Methods:

The primary outcome of the main study is the incremental change in circumcisions performed attributable to the respective demand creation interventions. Costs will be estimated for primary outcome with reference to the control group, in which we will continue to provide routine recruitment approaches. This will demonstrate how the costs vary depending on the mode of demand creation.

We shall adopt a societal perspective because of the ability to integrate diverse factors into the model and the role the public sector plays in HIV prevention and management. This approach incorporates all costs borne by the implementers in recruiting participants for services.

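### The stated reading of the ICER, that higher means less cost-effective, holds only for arms that cost more and achieve more than Control, and the protocol does not limit it to them

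*Protocol*

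**What the plan says.** All references are to the protocol.

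- **Costing Data Analysis: ICER estimation** takes incremental costs and "incremental effects (DALYs averted) (ΔE) attributable to IPC, DSO, IPC+DSO interventions, with reference to routine VMMC service delivery settings". It continues: "Each will be expressed in terms of an incremental cost effectiveness ratio (ICER; ΔC/ΔE". These ratios "shall be the key outcome measures of the model to determine the additional costs and benefits of each strategy over the other". A service-delivery version is also planned: "We shall estimate the ICER for additional proportion of men aged 25-39 years accessing VMMC sites as the primary service delivery outcome". After a line introducing formulae (not legible in the text available) comes the reading: "The higher the ICER the less cost effective the intervention program is".
- The same section plans an acceptability curve for each intervention by Monte Carlo simulation, to describe uncertainty, and refers to a range of willingness-to-pay values.
- **Costing VMMC in the Context of the Interventions (Sub-study 3)** expects to show both accrued costs and net savings for each strategy, and gives the purpose: "This information will support policy and program decisions, guideline formulation, and allocation of scarce resources to scale up effective demand creation approach(es".
- **Data Analysis**, under the costing aim (numbered Aim 2 there), says that cost-effectiveness will be judged by comparing the average or median cost per man circumcised across arms.

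No legible passage limits the ICER sentence to particular signs of cost and effect, or says how a dominated or dominant arm will be handled.

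**The concern.** A ratio of two differences can be read on a single scale only while both differences are positive. The sentence claims more. An arm that spends more than Control and circumcises fewer men has a negative ICER. Taken at its word, the sentence makes that arm more cost-effective than any arm that buys real additional circumcisions at a positive cost. An arm that saves money and circumcises more men is also negative, so the sign alone does not separate best from worst. Since the section foresees net savings, negative ratios from good arms are within what the protocol itself expects.

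There is a second, smaller difficulty. Effects and costs are defined against routine services only, yet the ICERs are meant to compare the strategies with one another. Ratios to a common Control do not do that.

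At stake is the reading of a result intended to inform scale-up. The primary comparison of uptake is not affected.

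**Working it through.** **1. Signs.** With ICER = ΔC/ΔE against Control:

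| ΔC | ΔE | ICER | Status | Does higher mean worse? |
|---|---|---|---|---|
| + | + | positive | trade-off | yes |
| + | − | negative | dominated | no: reads as better than every positive ICER |
| − | + | negative | dominant | no: same sign as dominated |
| − | − | positive | saves money, loses effect | no: a higher ratio means more saved per unit lost |

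The sentence is correct in one row of four. Within the dominant row it also misorders. Saving 100 with 10 DALYs averted gives −100/10 = −10; saving 100 with 20 averted gives −100/20 = −5. The second arm is strictly better, but its ICER is higher.

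The examples named under Sensitivity Analysis (overheads, staffing, resource use) are on the cost side. Raising the cost of a dominated arm makes its ICER more negative, so varying them would not expose the problem.

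**2. Between strategies.** Let IPC cost 1 unit more than Control and gain e₁, and let IPC+DSO cost 2 units more and gain e₂ > e₁ (a cost ratio assumed for illustration). The ratios to Control are 1/e₁ and 2/e₂. If e₂ < 2e₁, IPC+DSO has the higher ratio and reads as less cost-effective. The choice between the two nevertheless turns on (2 − 1)/(e₂ − e₁) set against the payer's threshold, which the ratios to Control do not show.

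**3. Precision of the effect.** The protocol gives no figure for how the ICER reading behaves. The nearest stated figure is the sample size, which fixes the precision of ΔE. For 30% v 40%, two-sided α 0.017 and 80% power, the pooled two-proportion formula gives 473 per arm. With continuity correction, (473/4) × [1 + √(1 + 4/(473 × 0.10))]² ≈ 493. Then 493 × 2.5 = 1232.5, matching the stated 1233.

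**4. How often a dominated arm would have the lowest ICER.** Inputs from the protocol: Locations per arm from Table 2 ("Totals | 11 | 11 | 11 | 12 | 45", in the order Control, IPC, DSO, IPC+DSO, total); 4,932 men, so 4932/45 = 109.6 per Location; Control uptake 30%; design effect 2.5 as stated, or 1 + 108.6 × 0.005 = 1.54 from the stated ICC. Assumptions not in the protocol: ΔC > 0 in all three arms, the effect measured as the uptake difference, and point-estimate ICERs ranked literally.

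Under these assumptions the lowest ICER is negative whenever any arm falls below Control. If k arms have no effect and the others are almost never below Control, the probability is 1 − 1/(k + 1):

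- no arm works (k = 3): 1 − 1/4 = 75%; simulated 74.7–74.9% over 400,000 trials per setting, whatever the cost ratio or design effect;
- one arm works, +10 points (k = 2): 1 − 1/3 = 67%; simulated 66.5–66.6%;
- two arms work (k = 1): 1/2 = 50%; simulated 49.9–50.1%.

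If all three arms gain 10 points, with design effect 2.5:

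- 11-Location arm v Control: SE = √[2.5 × (0.21 + 0.24)/1205.6] = 0.0305, z = 3.27, P(ΔE < 0) ≈ 0.0005.
- 12-Location arm v Control: SE = √[2.5 × (0.21/1205.6 + 0.24/1315.2)] = 0.0299, z = 3.35, P ≈ 0.0004.
- Sum over the three arms ≈ 0.0015, that is 0.15%; simulated 0.146%, and 0.005% with design effect 1.54.

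At +5 points in every arm the simulated figures are 4% (design effect 1.54) and 11% (2.5).

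**5. The other criterion.** With equal numbers of men, an arm with higher total cost and fewer circumcisions than Control has a higher cost per man circumcised, so it ranks below Control. The ICER sentence reads the same arm as better than any arm with a positive ratio. The two sections therefore pull in opposite directions for such an arm.

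**The case against.** A reader might infer that the protocol adopts a rule that names a dominated strategy most cost-effective in three trials out of four. The documents do not support that. The sentence is interpretive: nothing says that the arm with the lowest point estimate will be ranked first or recommended. The 75% is simply 1 − 1/4 for four exchangeable arms. It needs no effect in any arm and extra cost in every arm, and the protocol gives no cost figures; it even expects the unit cost of circumcision to fall as demand rises. At the effect for which the trial is sized, in all arms, the risk is negligible.

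There are also safeguards. An acceptability curve computed in the usual way, from the sign of net benefit, does not favour an arm that costs more and achieves less. The cost-per-man comparison places such an arm below Control. The stated use is to scale up effective approaches, and effectiveness is tested separately against Control with Bonferroni adjustment. The costing aim does ask for comparison among the interventions as well as with no intervention. Finally, the formulae just before the sentence are not legible, and a sign condition might stand there.

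These points remove the strong reading but leave the sentence. It carries no condition of its own, it interprets what the protocol calls the key outcome, and it is false in three of the four sign combinations. The acceptability curve is assigned to uncertainty and does not replace the ICER. This is a statement that is wrong as written, so it is not detail left to an analysis plan.

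It might also be inferred that the ICER should give way to net benefit as the key outcome. That is a preference; the defect does not require it.

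**Conclusion.** The point holds as a defect of wording with a real consequence for interpretation. The unconditional reading is valid only when ΔC > 0 and ΔE > 0. Outside that case it favours dominated arms, cannot separate them by sign from dominant ones, and conflicts with the cost-per-man criterion elsewhere in the protocol.

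The size depends on how many arms work. With literal ranking of point estimates and extra cost in every arm, a dominated arm would have the lowest ICER in about 75%, 67% or 50% of trials with none, one or two effective arms, and in at most about 0.15% if all three gain 10 points. These figures show what the sentence permits; they do not predict what the investigators would report. The matter is confined to the costing sub-study, but it should be corrected because that sub-study is meant to guide scale-up.

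**What to change.** In the ICER section of the costing plan:

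1. Limit the sentence to arms with ΔC > 0 and ΔE > 0.
2. Before any ICER is read, label each arm from the signs of ΔC and ΔE: dominated if it costs more and achieves less, dominant if it costs less and achieves more. Give no ranking by ICER to arms so labelled.
3. For the comparison between strategies, order the four arms by effect, remove dominated and extended-dominated arms, and compute each remaining ICER against the next less effective arm.
4. State how this relates to the average or median cost per man circumcised under Data Analysis, so that the two sections use one reconciled criterion.

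Net benefit over the planned threshold range may be reported alongside, but need not replace the ICER. Once dominance is labelled first, no arm dominated by Control on the estimates can be named best, so the figures of 75%, 67% and 50% become 0%.

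The cost is a few lines of analysis text. The same cost and uptake data and the same Monte Carlo runs are used. The only loss is that some arms will carry a dominance label where a single ratio would have stood.

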## Sensitivity Analysis

Variables included in the cost effectiveness analysis are not very stable because of parameter, methodological and structural uncertainties. Intuitively therefore, the ICER generated will have some degree of uncertainty, hence reducing its appeal for use in policy considerations. In view of this, sensitivity analysis will be conducted, to reveal the robustness of the ICER with respect to parameter changes. Scenario analysis involves changing the base case values with alternative values to examine changes in the ICER. The variables that can be changed include: overhead costs, staffing costs attributed to service delivery and variables for which there was the most uncertainty surrounding the resource use parameters.

# PHASE 5: ESTABLISHING ENDLINE MC UPTAKE/ESTIMATING IMPACT OF INTERVENTIONS

At Endline, we will review our Participants Master Log (Appendix 14) to identify those who did not go for VMMC at the 45 VMMC clinics participating in the study. We will use the telephone numbers obtained during enrollment to contact the participants. Those who say that they got circumcised but are not in our Participant Master Log, we will make an appointment and visit them at home, or another convenient location, to administer consent (Appendix 2C), conduct Endline interview (**Appendix 2D: Phone and In-Person Interview with Uncircumcised Men at Endline**) and verify their circumcision status. Those who report not having gone for VMMC will be asked why they did not go, and their response recorded in Appendix 2D. If more than one reason is given, the participant will be asked to rank the top three reasons from most to least important. As enrolled participants go for VMMC services, we will be recording in the study’s Participants Master Log that they have been circumcised. However, only those who go for VMMC at study-designated clinics where we have stationed Research Assistants to monitor uptake will be recorded in the Participants Master Log. Recognizing that some participants could choose to go for circumcision in non-study clinics, we will need to capture those ones as well. To do this, we will not call any person apart from men who are listed in our Participants Master Log. We will review VMMC program theater registers in non-study clinics located within the 12 districts where the study is being conducted and compare the names with those indicated on the Participants Master Log as having not gone for VMMC. For those where the three names of VMMC clients in theater registers match the three names in the Participants Master Log, we will contact them using the phone numbers registered in the Participants Master Log and NOT in VMMC theater registers. When calling, the TASCO participants who could have been circumcised at non-study clinics will be asked if they were enrolled in the study. If they were, we will schedule a visit at home and obtain consent and if willing, conduct endline survey and verify MC status; if not, they will not be contacted further.

Inclusion/Exclusion Criteria

Inclusion:

- - 1. Was enrolled in the main study
    2. Resident of the study village
    3. Did not go for circumcision per TASCO Study database

Exclusion:

1. Was not enrolled in the main study
2. Non-resident of study village

Has been circumcised per TASCO Study database

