**Sample size Determination**

Sample size for detecting the impact of the interventions on VMMC uptake

Unpublished data from an on-going demand creation study and an HIV community based study show an average of 30% circumcision prevalence in the target group (25-39 years); a corresponding refusal rate of 15% and loss to follow-up of 15%. Using an average MC uptake of 30%, an intra-cluster correlation coefficient (ICC) of 0.005, and a design effect of 2.5 in sample size formula for cluster studies, we estimated that in order to be able demonstrate at least a 33.3 % increase in the rate of VMMC among young adult men in intervention arms when compared to those in control arm with 80% statistical power, and Bonferroni adjusted two-sided $\alpha=(\frac{0.05}{3})=0.017$ following the implementation of study interventions , we will need a sample size of 4,932 men reached with the intervention.

The graph below (*Figure 1)* shows that an effect size equal to 33.3% increase in MC from 30% to 40% will require about 1233 participants per study arm (total 4932), while an effect size equal to 50% increase in VMMC from 30% to 45% will require 573 participants per study arm (total 2292).

Adjusting for refusal rate of 15% and a loss to follow up of 15%, suggests contacting 1603 per study arm resulting in a total of 6412 uncircumcised men aged 25-39 years.

Fig.1 shows a range of sample size requirements for detecting various percentage increases (effect sizes) in VMMC uptake due to the interventions assuming causal effect, and for an 80% power, a 1.7% significance level and a two sided test.

[figure not shown]

Figure 1: Sample Size Vs Percentage Increase in MC Uptake

Selection of Clusters (Locations):

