## Data Analysis:

***Aim 1:*** ***Compare the rate of uptake of VMMC services by men aged 25-39 years exposed to Inter-Personal Communication, Designated Service Outlets, and IPC+DSO.***

The main outcome measure of this study is VMMC uptake. To assess the rate of uptake of VMMC services by uncircumcised men aged 25-39 years, we will compare the proportion of men who accept to be circumcised across the intervention arms. Specifically, the proportion of men accepting to be circumcised in each of the three arms will be compared to the proportion accepting circumcision in the no intervention group. P-values will be adjusted for multiple comparisons using the Bonferroni method. In order to take into account the clustered nature of the data, we shall also employ statistical methods suitable for analysis of cluster-randomized trials, namely the multi-level logistic regression model via the generalized estimating equations (GEE) approach with a random intercept. The random intercept term will represent the differences in true log-odds between the Locations. Odds ratio of VMMC uptake comparing intervention groups to the control group with the same underlying uptake rate will be estimated. This model will simultaneously assess individual-level and Location-level factors associated with uptake of VMMC as well as the effect of the interventions. Most importantly, it will enable the assessment of the intervention at the level at which randomization occurred: the Location level.

As outlined above under Phase 4, we shall conduct an endline survey in all households with men aged 25-39 years to establish the post-intervention MC uptake, and for those circumcised, collect information on when and where they were circumcised. These will be compared with similar data collected at baseline, using the methods described in the paragraph above. In addition, we shall extract from our database information on age of participants receiving services in each Location/Cluster. We will also have a sense of effectiveness of each recruitment strategy from surrendered referral coupons and from responses to question 1 in Appendix 20 B, asked to men who come for MC and through Appendix 2, the number of men reported and/or verified as circumcised at endline. This information, collected from multiple sources and through multiple approaches, will be compared across different arms of the study.

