| **PHASE 5: ENDLINE SURVEY** | | | |
| Appendix 2C | Written Informed Consent Form for Enrollment and Verification of Circumcision Status at endline | | To administer consent to collect end-line information during revisits to sampled households.  Endline information used to determine the number of men circumcised during the study. |
| Appendix 2B | Enrollment Questionnaire and Circumcision Verification | | Interview men aged 25-39 years on top reason(s) for going or not going for VMMC and verify MC status. |

**Table 8:** Proposed Timelines for Set Up and Data Collection

|  | **Description of activities** | **Months from Start** | | | | | | | | | | |
| --- | --- | --- | --- | --- | --- | --- | --- | --- | --- | --- | --- | --- |
|  |  | **1-3** | **4-6** | | **7-9** | | **10-12** | | **13-15** | **16-18** | **19-21** | **22-24** |
| **Start up** | Submit protocol to CDC Atlanta: CDC-DGHA Science Office; IRB. Select study locations, randomize to intervention arms. ***Up to 6 Months depending on final ethics approval*** | **x** | **x** | |  | |  | |  |  |  |  |
|  | Conduct desk review to develop messages addressing MC barriers and facilitators (use this to develop draft Demand Creation Information Tool); develop SOPs; identify local support structures, prepare logistics such as printing study materials. ***Up to 4 Months*** | **x** | **x** | |  | |  | |  |  |  |  |
| **Phase 1** | Hire and train staff, conduct household survey; visit all households with men aged 25-39 years; interview them; verify their MC status to establish MC prevalence and determine denominator. ***Up to 3 Months*** |  |  | | **x** | |  | |  |  |  |  |
| **Phase 2** | Recruit and train RAs  Conduct formative research (IDIs & FGDs).  ***1-2 Months*** |  |  | | **x** | |  | |  |  |  |  |
| **Phase 3** | Analyze information on barriers and facilitators of MC from formative phase; update and finalize Demand Creation Information Tool; submit tool to CDC and Kenyan IRBs for review and approval.  Conduct baseline interview and verification of MC status  ***Up to 3 Months unless ethics approval of modification delays***. |  |  | | **x** | | **x** | |  |  |  |  |
| **Phase 4** | Data analysis and integration of messages  Identify and train recruiters on study design and recruitment strategies.  ***Approximately 1 Month*** |  |  | |  | | **x** | |  |  |  |  |

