|  | Implement the three interventions, including collecting information on costing and specimens for unlinked HIV testing. ***Approx. 9 Months*** |  |  | |  | | **x** | | **x** | **X** |  |  |
| **Phase 5** | Carry out endlline survey in all households with men 25-39 years uncircumcised at baseline; interview them; verify their MC status and use baseline data from men aged 25-39 years to determine the impact of the interventions. ***Approx. 3 Months*** |  |  | |  | |  | |  | **x** | **x** |  |
| **Cross-cutting** | Data entry, cleaning and analysis, report writing and manuscripts preparation. ***Ongoing up to 18 Months*** |  |  | | **x** | | **x** | | **x** | **x** | **x** | **x** |
|  |  | | | | | | | | | | | |
| **Sub-Study 4** | Develop SOPs; prepare logistics such as printing study materials. ***Approx. 2 Months*** |  | |  | |  | | **x** |  |  |  |  |
|  | Hire and train RAs. ***1 Month*** |  | |  | |  | | **x** |  |  |  |  |
|  | Enroll male participants in the study. ***Up to 6 Months*** |  | |  | |  | |  | **x** | **x** |  |  |
|  | Follow up male participants. ***Up to 8 Months*** |  | |  | |  | |  | **x** | **x** | **x** |  |
|  | Enroll female partners of the men in the study. ***Up to 6 Months*** |  | |  | |  | |  | **x** | **x** | **x** |  |
|  | Data entry and analysis; manuscripts preparation. ***Ongoing up to 12 Months*** |  | |  | |  | |  | **x** | **x** | **x** | **x** |

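### The protocol gives two conflicting rules for ascertaining circumcision at endline, a telephone follow-up and a household survey, so the primary uptake proportion has no single numerator

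*Protocol*

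**What the plan says.** The Data Analysis section names the outcome: "The main outcome measure of this study is VMMC uptake". The protocol then describes its endline collection in four places.

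- **Phase 5.** Staff start from the Participants Master Log and take the men not recorded as circumcised. "We will use the telephone numbers obtained during enrollment to contact the participants". Men who say they were circumcised are visited, interviewed and verified. Men who say they were not are asked for their reasons, and no verification is stated. Theatre registers of non-study clinics are also searched, but a match on all three names leads to a call to the number already in the Master Log. Only circumcisions at study-designated clinics with a stationed research assistant enter that log directly.
- **Data Analysis, Aim 1.** "we shall conduct an endline survey in all households with men aged 25-39 years to establish the post-intervention MC uptake". The text points back to Phase 4 for this survey, but Phase 4 describes none.
- **Table 8.** "Carry out endlline survey in all households with men 25-39 years uncircumcised at baseline", followed by interview and verification of status.
- **Table 7, Phase 5 rows.** The consent form is "To administer consent to collect end-line information during revisits to sampled households".

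The inclusion criteria add that men without a telephone give a friend's number. Phase 3 says the study captures a man's data only if he goes for circumcision within 3 months of enrolment. Phase 5 does not apply that window to circumcisions found at endline.

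**The concern.** The rules differ in mode (telephone or visit), in who is covered, and in who is verified. A man circumcised at a non-study clinic whose telephone does not answer counts as circumcised under the household rule and as uncircumcised under Phase 5. A man who wrongly says he is uncircumcised is corrected only where verification covers everyone.

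This is field procedure. A later analysis plan can choose among data sources, but it cannot recover visits that were never made. The Data Analysis section says that information from several sources will be compared across arms, and gives no rule for combining them.

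A second issue is possible imbalance. What is left for endline to find depends on what the clinics logged, and the directions men receive differ by arm. The DSO arms get a flyer naming sites, IPC men get a coupon listing sites, and control men get the general booklet. Capture could therefore differ by arm.

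**Working it through.** **Side by side**

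- Phase 5: enrolled men not logged as circumcised; telephone; visit and verification only for those reporting circumcision; no stated fallback if the call fails.
- Data Analysis: all households with men aged 25-39; household survey; date and place of circumcision collected.
- Table 8: households with men uncircumcised at baseline; interview and verification.
- Table 7: revisits to sampled households, which may only mean households in the sampled villages.

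The firm conflict is Phase 5 against the Data Analysis section and Table 8. Those last two also differ from each other in whom they cover.

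**The plan's own figure.** Inputs from Sample size Determination: "Using an average MC uptake of 30%, an intra-cluster correlation coefficient (ICC) of 0.005, and a design effect of 2.5", a target of 40%, and "for an 80% power, a 1.7% significance level and a two sided test".

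- Unadjusted n per arm = [2.387 × √(2 × 0.35 × 0.65) + 0.842 × √(0.30 × 0.70 + 0.40 × 0.60)]² / 0.10² = 473 (rounded up).
- With continuity correction: (473/4) × [1 + √(1 + 4/(473 × 0.10))]² = 493 (rounded up).
- Times the design effect: 493 × 2.5 = 1,232.5, rounded up to 1,233 per arm, as stated. The sample size is not in question here.

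With effective n = 1,233/2.5 = 493.2 per arm and alpha 0.05/3, power for 30% v 40% is 0.82 (normal test, no continuity correction).

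**Effect of incomplete capture.** Let p be true uptake, s the share of circumcisions done at non-study clinics, and c the share of those found at endline. Observed uptake = p × [1 − s(1 − c)]. The protocol gives neither s nor c. The values below are assumptions. The only nearby document figure is the 15% loss to follow-up, which would correspond to c = 0.85.

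*Equal s in both arms, true 30% v 40%.* For s from 0.1 to 0.3 and c from 0.85 to 0.50:
- the ratio stays at 1.33;
- the difference is 8.5 to 9.9 points;
- power is 0.70 to 0.81.

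*Unequal s, no true effect (30% in both arms), s = 0.20 control and 0.05 intervention.*
- c = 0.85: 0.30 × (1 − 0.20 × 0.15) = 29.1%; 0.30 × (1 − 0.05 × 0.15) = 29.8%; false difference 0.7 points; rejection rate 2.0% against 1.7% nominal.
- c = 0.70: 28.2% v 29.55%; 1.35 points; about 3%.
- c = 0.50: 27.0% v 29.25%; 2.25 points; about 5.5%.

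*Shares swapped.* The same differences appear with the opposite sign.

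*Unequal s, true 30% v 40%, c = 0.85.*
- s = 0.20 control and 0.05 intervention: 39.7% − 29.1% = 10.6 points.
- Shares swapped: 38.8% − 29.8% = 9.0 points.

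**The case against.** A reader might infer that the telephone route misses more circumcisions in the control arm and so inflates the intervention effect. The protocol does not support that.

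- Calls and register searches apply in the same way to every enrolled man.
- DSO men are told that all other sites still serve them, and IPC+DSO men are told of both kinds of site. The protocol plans a question for those who go elsewhere.
- DSO delivery includes private facilities and mobile services, and no section says each has a study assistant. Under-capture could therefore fall on the DSO arms and dilute the effect.
- Men in the IPC-only arm are not steered to DSO sites, so that mechanism says little about IPC v control.
- The non-study shares and the 70% and 50% reach are assumed.

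All of this stands. It limits the imbalance to a possibility of unknown size and sign.

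The protocol also has mitigation. It searches non-study registers, and the Aim 1 justification compares non-study facility data with the Master Log. Phase 1 collects locator information partly for endline return visits. The endline form is titled for both telephone and in-person use. This weakens any claim that the telephone is plainly the only route. It does not remove the conflict: Phase 5 follows a register match with a call to the same number, and it states no home visit after a failed call.

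Counting Table 7 as a third incompatible rule would also go too far, because its wording can mean households in the sampled villages. It only needs aligning.

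**Conclusion.** The contradiction stands and concerns the primary outcome. Phase 5 and the household-survey sections prescribe different field work and can give different uptake numerators, and no section says which governs. It should be resolved before endline collection starts.

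Differential loss by arm is a risk, not a finding. If capture is equal across arms, the ratio is unchanged and some power is lost. If it is unequal, the false difference is about 0.7 points at 20% v 5% non-study use and 85% reach. It rises to 2.25 points at 50% reach and reverses if the shares reverse. These figures treat telephone reach as the whole of endline capture and give the register search no separate credit, so they illustrate scale only.

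**What to change.** State one rule in Phase 5, the Data Analysis section, Table 7 and Table 8, applied identically in all four arms:

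- Every enrolled man uncircumcised at baseline and not logged as circumcised receives the household endline visit, with interview and, if he consents, verification of status.
- The telephone is used to book the visit. If the call fails, a home visit is attempted with the locator information already collected.
- The primary outcome is logged or endline-verified circumcision within the protocol's 3-month window from enrolment, with the date taken at the visit.
- Register matching stays as an additional source for men who are absent or decline examination.
- The cross-reference to Phase 4 in the Data Analysis section is corrected, and the household wording in Table 7 is aligned.

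The cost is a protocol amendment and more field effort than telephone follow-up alone. Table 8 already schedules about three months for a household endline survey, so the work falls within the planned period.
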